## 5 INVESTIGATIONAL PRODUCT

### 5.1 [I]Iodometomidate

[I]Iodometomidate was developed as a highly specific tracer for the characterization of adrenal masses. This tracer binds with high affinity to 11 $\beta$ -hydroxylase (CYP11B1) and aldosterone synthase (CYP11B2), two enzymes exclusively expressed in adrenocortical tissue. In an initial phase I/II study, 36 patients with an adrenal lesion and 14 patients with known metastatic adrenocortical carcinoma were investigated using 185 MBq [I]Iodometomidate. Both, adrenals and adrenocortical tumor tissue, were first detected within 60 min after injection of [I]IMTO, with very good delineation of the adrenals and the tumor lesions 4-6 hours after injection. Best target to background ratios were observed at 24 hours p.i. with specific uptake exclusively in the adrenocortical tissue. Both, renal elimination and hepatobiliary excretion with transient tracer accumulation in the gallbladder and the bowels, were noted. Only temporary tracer accumulation in the early phase was observed in the brain, liver and the kidneys.

According to the applied grading system, all tumors of the 16 patients with a benign adrenocortical lesion were graded as 1 (definite adrenocortical origin), 9 tumors of 14 patients with adrenocortical carcinoma were graded as 1, one tumor as 2a (probably adrenocortical), two as 2b (indeterminate, more probably non-adrenocortical) and one tumor was graded as 3. Of the non-adrenocortical lesions 3 of 20 lesions were characterized as 1 (one pheochromocytoma and two metastases), four tumors were scored as 2 (one 2a, two 2b) whereas the remaining 13 lesions were correctly graded as 3. Qualitative analysis resulted in a sensitivity of 89% and a specificity of 85%. Remarkable is the perfect sensitivity (100%) in the detection of adrenocortical adenomas. The uptake of [I]Iodometomidate in adrenocortical tissue was considerably high and specific, enabling successful radiotherapy of selected patients with advanced adrenocortical carcinoma using a related compound which has been radiolabeled with the  $\beta$ -emitter I ([I]IMTO) (4).

Observed adverse events were either unrelated to [I]Iodometomidate or caused by the addition of a solubilizer (Tween80), which was consequently replaced by ethanol. During long-term follow-up (> 2 years) no side effects attributable to the study were observed. The whole-body effective dose was calculated to be typically less than 3 mSv. Non-German sites will be permitted to use the tracer [C]Metomidate (MTO) instead of [I]Iodometomidate (IMTO) if available at the respective site and if in compliance with local regulatory authorities. The rationale is that there is no impact on the qualitative assessment (Visual score) which is the primary endpoint of the study. Whenever quantification (Uptake) is part of a secondary endpoint, a subgroup analysis will be performed.

## 5.2 Radiolabelling of the tracer and biodistribution

The radiosynthesis of [ $^{123}\text{I}$ ]Iodometomidate is performed by radioiododestannylation using an optimized and validated protocol. The tracer can be obtained within a very short reaction time of 3 min in >90% radiochemical yield. Purification is performed by radio-HPLC followed by formulation in PBS/20%ethanol and sterile filtration.

Labelling of [ $^{123}\text{I}$ ]Iodometomidate for in-house-production will be performed by one study centre (Würzburg) which has access to laboratories meeting GMP standards and holds a manufacturing authorization for [ $^{123}\text{I}$ ]Iodometomidate. The study centre Würzburg plans to start the FAMIAN-Trial as soon as possible.

The remaining study centres will be provided with [ $^{123}\text{I}$ ]Iodometomidate by the company MAP Medical Technologies Oy ([name], [name], Finland).

Additionally, the alternative supply of [ $^{123}\text{I}$ ]Iodometomidate to the study centre Würzburg by MAP Medical will be allowed to bridge temporary shortage of devices (i.e. maintenance) or personnel (holidays, illness).

Vice versa it will be possible for all centers to send their patients to Würzburg solely for the [ $^{123}\text{I}$ ]Iodometomidate scan: In this case the sponsor will provide for a reasonable accommodation for the necessary overnight stay for patient - and partner if requested.

Non-German sites will be permitted to use [ $^{11}\text{C}$ ]Metomidate (MTO) instead if available through in-house-production and after having obtained consent of the local authorities.

## 5.3 FDG

The radiopharmaceutical [ $^{18}\text{F}$ ]Fluorodeoxyglucose (FDG) has been described already in the late 1970s as surrogate marker for tissue glycolysis which was subsequently used to non-invasively detect and characterize malignant tumors. The positron emitter  $^{18}\text{F}$  enables 3D imaging of the entire body using positron emission tomography (PET). PET, in combination with spiral CT, represents one of the most sensitive and specific imaging modalities and a mainstay diagnostic test for cancer imaging (18).

The German study centres will be provided with FDG from several distributors, which hold a marketing authorization for FDG:

| Study centre   | Distributor                                                                         |
|----------------|-------------------------------------------------------------------------------------|
| Würzburg       | ZAG Zyklotron AG
[name]
[name] |
| Leipzig        | Universitätsklinikum Leipzig AöR
[name]
[name]                  |
| Mainz, München | Advanced Accelerator Applications Germany
[name]
[name]       |
| Berlin         | Life Radiopharma Berlin GmbH
[name]
[name]                   |
| Essen          | Universitätsklinikum Essen A.d.ö.R.
[name]
[name]             |

## 6 DIAGNOSTIC STUDIES

### 6.1. FDG-PET, FDG-PET/CT

In all participating centres, patients will have FDG-PET scans using state-of-the-art hybrid PET/CT devices. Within the FAMIAN Protocol only low dose CT will be performed, however, in case of clinical need, full dose CT can be performed for diagnostic purposes at the discretion of the investigator to avoid additional radiation exposure by a separate imaging procedure. CT data will be also used for attenuation correction and anatomic localization of lesions detected by PET. Patients will fast for at least 6 hours before the PET/CT scan, and blood glucose levels will be measured before the administration of FDG. Blood glucose levels have to be below 150 mg/dl. Static emission imaging will be performed 60 minutes (aimed window: 55 to 75 min, a longer interval due to clinical requirements is acceptable) after i.v.-injection of FDG according to PET/CT scanners and guidelines (e.g. EANM PET/CT: EANM procedure guidelines for tumor imaging: version 2.0; Bundesamt für Strahlenschutz: Bekanntmachung der aktualisierten diagnostischen Referenzwerte für nuklearmedizinische Untersuchungen, 25.Sept.2012). Emission data will be corrected for random, dead time, scatter and attenuation.

### 6.2 [I]Iodometomidate-SPECT

[I]IMTO will be prepared as described above (5.2). Imaging will be performed with state of the art gamma cameras and acquisition settings adequate for Iodine. The settings and protocols indicated below for the site Würzburg are exemplary only, comparable protocols will be utilized by participating centres. Thirty minutes before injection of the radiotracer, radioiodine uptake into the thyroid gland will be blocked by oral administration of 600 -1200 mg sodium perchlorate. Thyroid blocking will be continued for 1-3 days using 3 x 460 mg sodium perchlorate per day. For Non-German sites the use of potassium iodide or other perchlorate preparations will be allowed instead of sodium perchlorate. After receiving 185 MBq [I]IMTO i.v., planar scans of the whole body will be acquired 4 h post injection using a standard technique (Würzburg: Siemens Symbia dual headed large field-of-view gamma camera, energy window 159 keV ± 7,5%, bed speed ("scan velocity") 20 cm/min, matrix 256 x 1024, medium energy parallel-hole collimator). All patients will also receive SPECT/CT imaging between 4 and 6 hours post injection (Würzburg: SPECT/CT will be performed using a Siemens Symbia T2 dual-headed large field-of-view gamma camera combined with a dual-detector CT, energy window of 159 keV ± 7,5%, a rotation of 180° with 3° angular steps (= 2 x 60 frames) at 30 s per projection, 128 x 128 matrix size, slice thickness 4.8 mm, medium energy collimator). Transmission will be measured by low-dose CT (Würzburg: 130 kV and 17 mAs, reconstructed slice thickness 5 mm, B08s kernel for attenuation correction, B30S kernel for visual interpretation and image fusion). SPECT data will be corrected for attenuation and reconstructed iteratively using the OSEM algorithm (Würzburg: 6 subsets, 6 iterations, 3D smoothing 8 mm). As an option, planar scans and SPECT/CT may be repeated 24 h post injection (delayed scan).

### 6.3 Centralized Imaging Review

The central imaging board is located at the University Hospital Würzburg. A multidisciplinary panel consisting of an endocrinologist, a radiologist and a nuclear medicine physician, accompanied by a statistician, will review all whole-body planar scans, PET, SPECT and CT scans blinded to clinical information. The visual interpretation criteria include a scoring system (1-5). A positive IMTO lesion is defined according to standardized criteria as focal or diffuse uptake in projection of the adrenal tumor higher than surrounding background activity based on planar and SPECT imaging (1: strongly positive, adrenocortical origin; 2: moderately positive, indicative for adrenocortical origin; 3: indeterminate; 4: mildly positive, unlikely adrenocortical origin; 5: negative, no adrenocortical origin).

Regarding FDG-PET scans, intensely FDG-avid lesions are scored as malignant (1), moderately FDG-avid lesions as more likely malignant (2), as indeterminate (3), mildly FDG-avid (4, more likely benign) or negative (5, definitely benign). In addition, semiquantitative analysis of tracer retention will be performed using tomographic images and 5 mm regions of interest for PET or 20 mm regions of interest for SPECT. ROIs are drawn in the area of the hottest pixel.

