#### 8.1.1 Primary variables and measures

Gold standard: An expert pathologist will classify the incidentaloma of a patient based on histopathology of surgical specimens. All removed neoplasias will be classified according to histopathological criteria. Primary classification will be all neoplasias AA or at least one neoplasmia non-AA.

Diagnostic tests: The tumors will be characterized as either positive or negative concerning FDG/Iodometomidate uptake leading to 4 different categories. The primary diagnostic test variables subsume to the indicators “all neoplasias of a patient FDG-PET negative” and “all neoplasias of a patient Iodometomidate positive”.

The diagnostic measures of primary interest are specificity, sensitivity and likelihood ratio of a positive diagnostic AA test using histopathology of the surgically removed tumor as gold standard for the differential diagnosis. Thereby the AA test uses the combined FDG-PET and Iodometomidate imaging: AA+ is defined for each neoplasmia as FDG-PET negative and Iodometomidate positive. The primary clinical outcome is the correct non-invasive diagnosis (using the combined AA test) of histologically verified adrenocortical adenoma and verified neoplasmia different from adrenocortical adenoma (for the estimation of the sensitivity and the specificity of the combined AA test).

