#### 2) Pathophysiological Principle

F-Fluorodeoxyglucose (FDG) is a radiolabelled glucose analogue which is taken up by cells using glucose as primary energy source. Glucose use is increased in many malignant tumors and also in inflammatory processes resulting in an increased FDG uptake. After intravenous injection, FDG is quickly cleared from the blood pool via glucose transporters located in the cellular membrane. Within cells, FDG undergoes rapid phosphorylation to fluorodeoxyglucose-6-phosphate by the enzyme hexokinase II and is retained in the cell (trapping). Due to the various uptake patterns of FDG in adrenal tumors observed in past series, we hypothesize that high FDG uptake is a prerequisite of malignant adrenal tumors (malignant primaries, adrenal metastasis), whereas benign tumors (i.e., adenoma, incidentaloma) are associated with missing or mild retention of FDG.

IMPORTANT: Cellular uptake of FDG is insulin-dependent and therefore influenced by food intake, the nutritional condition of the patient and presence of diabetes mellitus.

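### Section 6.3 calls any metomidate uptake above background positive, although its own score 4 reads such a lesion as unlikely adrenocortical; FDG scores and score 3 are not mapped to the binary call.

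*Protocol*

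**What the plan says.** Protocol 6.3 gives the visual reading rules of the central panel. For iodometomidate it states a positivity rule, "focal or diffuse uptake in projection of the adrenal tumor higher than surrounding background activity based on planar and SPECT imaging", and attaches a 1-5 scale. Scores 1 and 2 point to adrenocortical origin and the middle category is "3: indeterminate". The last two are "4: mildly positive, unlikely adrenocortical origin; 5: negative, no adrenocortical origin".

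For FDG, 6.3 gives a 1-5 scale only. Scores 1 and 2 are on the malignant side, and the remaining lesions are scored "as indeterminate (3), mildly FDG-avid (4, more likely benign) or negative (5, definitely benign". No sentence says which FDG scores count as positive or negative.

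Protocol 8.1.1 requires a binary result on both tracers: "The tumors will be characterized as either positive or negative concerning FDG/Iodometomidate uptake leading to 4 different categories". AA+ is FDG-negative together with iodometomidate-positive. Section 5.1 names the visual score as the primary endpoint, and all four hypotheses in 8.2 are stated in terms of AA+ or AA-.

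Two places bear on mild FDG uptake without setting a cut-off. Section 1.1 expects adenomas to have low FDG uptake. The FDG procedure in 17.3.2 contrasts malignant tumours with benign ones: "whereas benign tumors (i.e., adenoma, incidentaloma) are associated with missing or mild retention of FDG".

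**The concern.** The iodometomidate rule and the iodometomidate scale give opposite answers for the same lesion. Score 4 is called mildly positive, so it satisfies the background rule, yet the panel has recorded that adrenocortical origin is unlikely. Followed as written, the rule lets an FDG-negative, probably non-adrenocortical lesion enter AA+, which is the claim that the lesion is a cortical adenoma.

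The FDG side has a different fault: a required conversion from five scores to two is not stated. Score 3 is a predefined reader category on both scales, so it will be used, and neither scale gives it a side.

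At stake is the index test of the confirmatory hierarchy. If the score-to-binary conversion is settled only once scores and histology can be seen together, the cut-off can be chosen to suit the result, and the error level of test 1 is no longer protected.

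**Working it through.** **1. Apply the text to each score.**

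| Score | Iodometomidate: background rule | Iodometomidate: scale label | FDG: rule | FDG: scale label |
|---|---|---|---|---|
| 1 | positive | adrenocortical | none stated | malignant |
| 2 | positive | points to adrenocortical | none stated | more likely malignant |
| 3 | depends on uptake; scale gives no side | indeterminate | none stated | indeterminate |
| 4 | positive | **unlikely adrenocortical** | none stated | more likely benign |
| 5 | negative | not adrenocortical | none stated | negative, benign |

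The contradiction is in the iodometomidate row for score 4. The gaps are score 3 on both scales and the whole FDG conversion. If the cuts are treated as open, iodometomidate positive could be 1-2, 1-3 or 1-4, and FDG negative could be 5, 4-5 or 3-5. That gives 3 × 3 = 9 versions of AA+.

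**2. Direction.** Moving iodometomidate score 4 (or 3) to positive adds AA+ calls: specificity falls or stays, sensitivity rises or stays. Restricting FDG-negative to score 5 removes AA+ calls: sensitivity falls or stays, specificity rises or stays. The two act in opposite directions.

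**3. Reproduce the plan's figures for test 1 (8.3).** Inputs from 8.2 and 8.3: null specificity 0.90, target 0.98, two-sided 5% (upper tail 0.025), non-AA share 40%, 195 assessed.

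Let X be the number of false positives among n non-AA patients. Test 1 rejects if X ≤ c, where c is the largest value with P(X ≤ c | n, 0.10) ≤ 0.025.

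- n = 70: P(X ≤ 2) = 0.0242, so c = 2. Power is P(X ≤ 2 | 70, 0.02) = 0.835. At n = 69, c = 1 and power is 0.597. The stated minimum of 70 is reproduced.
- Expected non-AA patients: 195 × 0.40 = 78. P(X ≤ 2 | 78, 0.10) = 0.0126, so c = 2. Power is P(X ≤ 2 | 78, 0.02) = 0.795.
- Averaged over the binomial number of non-AA patients at N = 195, power is 0.796, against 80% stated.
- 195/0.9 = 217, against 220 stated; 220/0.4 = 550.

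**4. How little reclassification test 1 can absorb.** A third false positive gives a tail probability of 0.071 at n = 70 and 0.041 at n = 78. Both exceed 0.025, so with two false positives already present, one further non-AA lesion moved to AA+ loses the test.

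**5. Illustration, rates above 2% assumed.**

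| False-positive rate | Power, n = 70 | Power, n = 78 |
|---|---|---|
| 2% | 0.835 | 0.795 |
| 3% | 0.649 | 0.584 |
| 4% | 0.466 | 0.392 |
| 5% | 0.314 | 0.246 |

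**6. Evidence in the protocol that the grading cut matters.** Section 5.1 reports an earlier study on a different grading scale. Of 20 non-adrenocortical lesions, 3 were grade 1 (3/20 = 15%) and four more were grade 2 (7/20 = 35%; the sub-grades listed add to three, which would give 6/20 = 30%). These are single-tracer figures and do not estimate the false-positive rate of the combined test.

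**7. Why unreadable scans should not count as AA-.** Suppose readable scans have exactly 90% specificity and an assumed 20% of non-AA scans are unreadable but counted AA-. The false-positive rate becomes 0.80 × 0.10 = 0.08, and P(X ≤ 2 | 78, 0.08) = 0.046. Test 1 then rejects 4.6% of the time instead of at most 2.5%, with no real gain in specificity.

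**The case against.** A statistical analysis plan or reading charter, not shown, may hold the cut-offs, and a protocol may leave such detail to it. That is fair for the FDG conversion and for score 3 taken alone. It does not cure the iodometomidate rule: the protocol states a rule that conflicts with its own scale, and a later document with sensible cut-offs would contradict the protocol.

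A reader might infer that both scales are contradicted, with FDG-negative meaning score 5 only. The documents do not support that. No FDG rule is stated, so there is nothing to contradict; score 5 merely carries the word. Sections 1.1 and 17.3.2 point to mild uptake belonging with negative.

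A reader might also infer that following the text literally (iodometomidate 1-4, FDG 5) lowers both sensitivity and specificity. This is not established, because the two halves pull in opposite directions and the documents give no data on the size of either.

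Finally, the panel reads blinded to clinical information, and nothing in the protocol provides for choosing a cut-off after linkage to histology. So bias is not shown. The exposure is that the protocol does not close the choice, and blinded scoring does not by itself prevent a later choice of cut-off.

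**Conclusion.** The point holds in this form. The iodometomidate positivity rule in 6.3 is wrong as written because it makes score 4 positive against the label of that score. For FDG, and for score 3 on both scales, the conversion that 8.1.1 depends on is not stated. The index test of the confirmatory hypotheses is therefore not uniquely defined.

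The certain part of the size is the fragility of test 1: 2 false positives are allowed at 70 or at 78 non-AA patients, and a third loses significance. The fall in power from 0.80 to 0.39 at n = 78 rests on an assumed rise in the false-positive rate from 2% to 4%; it shows scale and is not a forecast. The net change in sensitivity and specificity is unknown. The planned 195 assessed and 220 recruited patients need not change once the cuts are fixed.

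**What to change.** - In 6.3, replace the above-background sentence by one score cut-off per tracer that agrees with the labels: iodometomidate positive = 1-2, FDG negative = 4-5, AA+ only if both hold. Cross-refer to it in 8.1.1. These cuts follow the labels and the remarks on FDG uptake in 1.1 and 17.3.2; the sponsor should confirm them.
- Treat a readable score 3 as not meeting its criterion, hence AA-. This favours specificity and the probability of AA- given ACC, so add sensitivity analyses with score 3 counted as AA+ and with score 3 excluded.
- Handle non-diagnostic or missing scans as incomplete assessments, in line with the assessable-endpoint rule in 8.2 and the 10% allowance in 8.3, not as AA- in the primary analysis. Report their number by histology group.
- Fix all of this before the central reads are linked to histology.

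Cost: one paragraph, a few extra tables, and possibly slightly lower sensitivity because indeterminate lesions count as AA-.

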## 7 TRIAL PROCEDURE

### 7.1 Screening

All patients with an indeterminate adrenal mass > 3 cm will be screened for inclusion and exclusion criteria by their physicians. Eligible patients will be handed out a patient information sheet. Imaging data documenting an adrenal tumor according to the inclusion criteria should not be older than 3 months.

#### 7.1.1 Informed Consent

The trial subject will have the opportunity to read the patient information sheet and consider his/her decision before dating and signing the document, and will be given a copy of the signed document. No patient will be able to enter the study before his/her informed consent has been obtained. Patients will be informed that they may withdraw their consent to participate at any time of the trial without giving the reason for it. The patient will be informed that choosing not to participate or to withdraw the consent will not affect his/her subsequent medical treatment or relationship to the treating physician.

#### 7.1.2 Enrolment and screening visit

Once written informed consent has been obtained, the patient will be enrolled in the study (**Visit 1**). Baseline evaluations should be performed within 4 weeks after inclusion (i.e. written informed consent). Screening and baseline evaluations include:

- Patient informed consent prior to any study related procedures
- Documentation of height and weight
- Documentation of detailed medical history
- Documentation of current medication
- Routine laboratory tests (serum creatinine, serum urea, glomerular filtration rate (MDRD), blood count, serum aspartate aminotransferase, alanin aminotransferase, alkaline phosphatase, gamma glutamyl transferase). If laboratory tests have been performed within two weeks of screening they do not have to be repeated.
- Evaluation of inclusion and exclusion criteria
- Recovery of imaging slides
- Physical examination
- Documentation of historical hormonal assessment (*Table 1*)

- 24 hours urine collection for steroidobolomics (not relevant for inclusion/exclusion of patients): If a sample of a 24h urine collected no earlier than 3 months before inclusion is stored at site (i.e. for Ens@t) then a portion of this can be sent.
- Pregnancy test (in women of child bearing potential): Any pregnancy test is allowed. However, sponsor will provide urinary pregnancy tests for the convenience of the sites.

For the safety of the patients, there will be no exceptions to eligibility requirements at the time of entering the diagnostic phase of the study.

